### Primary and secondary outcomes

The primary outcome will be the accuracy assessed by diagnostic performance parameters, such as sensitivity, specificity, positive predictive value (PPV), negative predictive value (NPV), receiver operating characteristics (ROC) curve, and area under the curve (AUC). Radiologists will prospectively provide a single BI-RADS classification for each exam, where a BI-RADS score of 1–3 will be considered ”benign” and 4-5 ”malignant”. The final BI-RADS score (BI-RADS 1–5), based on imaging, will be compared with the BI-RADS score given by the screening program. The accuracy assessed by diagnostic performance parameters will be assessed after the next screening round after approximately 2 years.

Secondary outcomes will be quality of life (QoL), days until final diagnosis, cost-effectiveness, and experienced patient anxiety during a follow-up of 18 months. Three validated questionnaires will be presented at six different time points (at study inclusion; after 2 and 4 weeks; and after 6, 12, and 18 months). QoL will be assessed by the Dutch version of the EuroQol five-dimension, five-level (EQ-5D-5 L) questionnaire, including a visual analog scale (EQ-VAS). This questionnaire is a preference-based instrument used to value health states [11]. The Dutch tariff for the EQ-5D-5L questionnaire, as established by Versteegh et al., will be used to calculate utility scores per health state [12]. Then the quality-adjusted life years (QALYs) will be modeled based on these utility scores. Resource use related to diagnostics will be collected during the trial.

Health-related anxiety, both state and trait anxiety, will be measured by the Dutch version of the State Trait Anxiety Inventory (STAI-DY-1 and STAI-DY-2) questionnaires. Each STAI has 20 items and will be rated on a 4-point Likert scale, scoring 20–80 points per STAI. A higher score corresponds to a higher anxiety level [13].

For the QoL and STAI scores, inter- and intra-patient differences over time from baseline will be compared including those between the intervention and control group. The scores will also be compared between the women with a follow-up exam after 6 or 12 months and those without this follow-up. Figure 1 shows the outcomes defined by the five outcome elements described by Saldanha et al. [14].

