### The control group: usual care with conventional breast imaging

Women undergoing standard of care will have their screening FFDM re-evaluated, adding (special) FFDM views, DBT, or US if deemed necessary. In FFDM and DBT, the breast is compressed between a paddle and detector plate. The laterality of the breast and views per breast depend on the judgment of the radiologist. At least one additional view of the recalled side will be performed. Tissue sampling (CNB, VAB, FNAC) can be recommended to support or to invalidate suspicious findings on imaging. In case of inconclusive findings, the radiologist can consider follow-up in 6 and/or 12 months or single breast MRI. The use of CESM is not permitted in this study arm.

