### The experimental group: contrast-enhanced spectral mammography

CESM is based on visualizing angiogenesis in tumor tissue using dual-energy mammography [15]. Prior to image acquisition, an intravenous catheter will be placed in the antecubital vein, after which its patency will be checked by a saline test bolus. A non-ionic, low-osmolar contrast agent consisting of either iopromide (Ultravist® 300, Bayer Healthcare, Berlin, Germany) or iobitridol (Xenetix® 300, Guerbet, Villepinte, France) will be administered at a dose of 1.5 mL/kg body weight. If an automatic injector is used instead of manual administration, the injection rate will be 2.5–3 mL/s, followed by a saline flush. Image acquisition is started after at least 2 min after contrast administration [16]. Although there is a limited risk of complications, such as hematoma or incorrect catheter placement, a previous retrospective study showed that the risks of adverse reactions to the contrast agents and contrast-induced nephropathy are negligible [17]. Two days after CESM, the patient file will be consulted to investigate whether any late (serious) adverse reactions to the contrast agent have occurred that need medical treatment.

Similar to FFDM, the breasts are positioned between a mammography paddle and detector plate, and the four standard views are made: a cranio-caudal (CC) and mediolateral oblique (MLO) view of each breast. Special views can be requested by the reviewing radiologist. A typical CESM exam consists (per breast exposure) of two images: a low- and a high-energy image, which are acquired within seconds [18]. These images are used in post-processing to acquire the recombined image, which shows areas of contrast accumulation (Fig. 2). The CESM image acquisition needs to be completed within 10–12 min after contrast administration [19]. As in the control group, US, tissue sampling, MRI, and follow-up can be considered in case of inconclusive findings.

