### Establishment of final diagnosis (the reference standard)

For the control group, final diagnoses of the (recalled) breast lesions can be divided into four categories [3, 5]: (1) simple cysts; (2) superposition densities; (3) solid, benign masses; (4) (invasive) breast cancer or ductal carcinoma in situ (DCIS). The first three groups are defined as benign findings. To ascertain a final diagnosis of (1), targeted US is performed, followed by cyst aspiration and a second FFDM of that breast to confirm that the lesion has disappeared. Final diagnosis of (2) requires a minimum of one special view or DBT, including targeted US. To rule out false negative (FN) findings, 6 and/or 12 months follow-up or breast MRI can be considered. Final diagnosis for categories (3) and (4) is acquired with US-guided or stereotactic tissue sampling. If cancer or DCIS is diagnosed, the subject will have a ”true positive” (TP) finding. In subjects where no breast cancer or DCIS is diagnosed, the follow-up period of 2 years will determine the true disease status. If no interval cancers have been detected and the subject has not been recalled in the subsequent screening round, the case will be considered a ”true negative” (TN).

In the CESM group, diagnoses are acquired slightly differently. For (1), CESM will show an ”eclipse sign” which is pathognomonic for cysts [3]. No further action is needed. For category (2), a negative CESM exam with no suspect lesion on both low-energy and recombined images rules out (pre)malignant lesions due to CESM’s high negative predictive value [3, 5]. To acquire final diagnoses of (3) and (4), CESM and targeted US are performed including tissue sampling for pathological confirmation.

Since most benign recalls are caused by cysts or superposition densities, the investigated intervention will most likely result in fewer additional exams and tissue samplings among these recalls [3, 5]. Moreover, follow-up exams can be omitted, which is more patient-friendly, and hypothetically, more women will attend the subsequent screening round when they are examined with CESM.

A flow chart is presented in Fig. 3, summarizing the study design, the randomization process, and the establishment of the different diagnoses.

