### Sample size calculation

Prior research showed a specificity of FFDM of 40% in this population [5]. To enable detection of a clinically relevant increase of specificity by 15% (from 40% to 55%), 176 patients without malignant disease per group are required (power 80%, alpha = 5%). The prevalence of malignant lesions in women recalled from the breast screening program is about 30%; thus, 70% have benign lesions. Therefore, a total of 251 women per group (176/0.7) has to be included. To account for 5% loss to follow-up, the final number of patients to be included is 528 (502/0.95). The calculations were done with OpenEpi [20].

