Second, the patients’ mental state during the recall and diagnostic work-up is thoroughly assessed by validated questionnaires. Due to the higher diagnostic performance of CESM, especially in terms of reducing the number of false positive findings, it is expected that in the intervention arm fewer additional exams will be performed, such as follow-up after 6 or 12 months, or breast MRI. These additional exams cause a delay in the assessment of final diagnosis and increase health care costs; plus we hypothesize that this will influence a patient’s mental state during these months. Finally, the study design allows for a cost-effectiveness analysis, showing us the impact on health care costs of both strategies during this period. We hypothesize that using CESM as a work-up tool is more efficient and cost-effective than following current standard care. If proven to be cost-effective, an important hurdle is taken toward acquiring reimbursement by health insurance companies for CESM, which at present frustrates the further introduction of CESM worldwide.

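### The comparison of QoL and anxiety by follow-up exam puts nearly all cancer patients in the comparator, so it mixes waiting with a cancer diagnosis

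*Protocol article*

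**What the plan says.** The contrast is set in Primary and secondary outcomes, directly after the comparison of the randomised arms: "The scores will also be compared between the women with a follow-up exam after 6 or 12 months and those without this follow-up". It applies to both QoL and STAI. No limit by final diagnosis is given. The Statistical analysis section plans mixed linear models for QoL and anxiety, does not mention this contrast, and names no diagnosis term.

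Who receives follow-up, and how cancer is established, is described elsewhere in Methods:

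- Control arm: "In case of inconclusive findings, the radiologist can consider follow-up in 6 and/or 12 months or single breast MRI".
- CESM arm: "US, tissue sampling, MRI, and follow-up can be considered in case of inconclusive findings".
- Reference standard, control arm, under superposition densities (a benign category): "To rule out false negative (FN) findings, 6 and/or 12 months follow-up or breast MRI can be considered".
- Cancer or DCIS (category 4), control arm: "Final diagnosis for categories (3) and (4) is acquired with US-guided or stereotactic tissue sampling".
- Cancer or DCIS, CESM arm: "To acquire final diagnoses of (3) and (4), CESM and targeted US are performed including tissue sampling for pathological confirmation".

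On the cancer share, the sample size section states: "The prevalence of malignant lesions in women recalled from the breast screening program is about 30%; thus, 70% have benign lesions". The Background says that about six in ten recalled women prove not to have breast cancer, which implies about 40% with it.

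The Discussion gives a likely motive. Of follow-up and MRI it says: "These additional exams cause a delay in the assessment of final diagnosis and increase health care costs". It adds the authors' hypothesis that this affects women's mental state in the meantime.

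**The concern.** Whether a woman has a 6- or 12-month exam is decided after randomisation, from her imaging. The women without such an exam are therefore two very different groups: those cleared promptly, and those diagnosed with cancer and moving on to treatment. If the contrast is read as the burden of waiting, the second group is the wrong yardstick, because its scores after diagnosis reflect the disease as well.

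Using change from baseline does not help. According to the Informed consent and randomization protocol section, the first questionnaires are completed ahead of all study procedures, and so before the work-up gives a diagnosis. Any effect of a cancer diagnosis lies wholly inside the change score.

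The contrast is also entangled with arm, since the Discussion expects fewer follow-up exams in the CESM group. At stake is the interpretation of this one supplementary result.

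**Working it through.** **Plan's own figures.** None is stated for this contrast. The total used below does reproduce: 176/0.7 = 251.4, so 251 per group; 2 × 251 = 502; 502/0.95 = 528.4, printed as 528.

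**Inputs from the article.** N = 528; cancer share P = 0.30 (Sample size calculation) or 0.40 (Background).

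**Assumed inputs.**

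- Share of women with a follow-up exam, f = 5% to 30%.
- Cancer share within that group, l = 0% to 5%.
- True effect of waiting, w = 3 STAI points compared with women cleared at once.
- Effect of a cancer diagnosis, c = 5, 10 or 15 STAI points. The scale runs from 20 to 80, and higher is more anxious.
- Equal baselines, and one constant value of c for state and trait scores and for all time points after diagnosis.

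**Step 1: expected cancers.** 528 × 0.30 = 158; 528 × 0.40 = 211.

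**Step 2: where they fall.** The share of all cancers that sit in the comparator is 1 − f·l/P. The lowest value, at f = 0.30, l = 0.05 and P = 0.30, is 1 − 0.015/0.30 = 0.95. The comparator thus holds 95% to 100% of the cancers.

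**Step 3: composition of the comparator.** q = (P − f·l)/(1 − f).

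- Lowest: (0.30 − 0.0025)/0.95 = 0.313.
- Highest: 0.40/0.70 = 0.571.

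**Step 4: expected contrast, follow-up minus no follow-up.** D = w(1 − l) − c(q − l). The sign reverses when c exceeds w(1 − l)/(q − l).

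Example with P = 0.30, f = 0.10, l = 0: 158.4 cancers among 475.2 women, so q = 0.333. At c = 10, D = 3 − 3.33 = −0.33. The break-even value is c = 3/0.333 = 9.0.

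Results for l = 0 and w = 3:

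| P | f | q | D, c = 5 | D, c = 10 | D, c = 15 | Break-even c |
|---|---|---|---|---|---|---|
| 0.30 | 0.05 | 0.316 | +1.42 | −0.16 | −1.74 | 9.5 |
| 0.30 | 0.10 | 0.333 | +1.33 | −0.33 | −2.00 | 9.0 |
| 0.30 | 0.20 | 0.375 | +1.12 | −0.75 | −2.63 | 8.0 |
| 0.30 | 0.30 | 0.429 | +0.86 | −1.29 | −3.43 | 7.0 |
| 0.40 | 0.05 | 0.421 | +0.89 | −1.21 | −3.32 | 7.1 |
| 0.40 | 0.10 | 0.444 | +0.78 | −1.44 | −3.67 | 6.8 |
| 0.40 | 0.20 | 0.500 | +0.50 | −2.00 | −4.50 | 6.0 |
| 0.40 | 0.30 | 0.571 | +0.14 | −2.71 | −5.57 | 5.3 |

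With l up to 5% as well, the full ranges are +0.1 to +1.5 (c = 5), −2.7 to +0.2 (c = 10) and −5.6 to −1.1 (c = 15). Break-even runs from 5.3 to 10.8 points.

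**Step 5: after restriction.** With no cancers in either group, q = l = 0 and D = w = +3.0. The women available are 528 × 0.70 = 370 or 528 × 0.60 = 317, before any loss to follow-up.

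**The case against.** The sentence is a one-line announcement in a journal article. Population, covariates and status are normally fixed in the full protocol or analysis plan, neither of which is shown, and a benign-only restriction could stand there. That is fair as to covariates and labelling. It is less persuasive on the comparator, because the article does name one: everybody without the follow-up exam.

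Two stronger readings are tempting, and the article supports neither.

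- A reader might infer that the trial's conclusion on patient anxiety is compromised. It is not. The sentence just before compares the randomised arms on change from baseline, and the secondary objectives are framed as a comparison of strategies. No objective or conclusion is tied to the follow-up contrast.
- A reader might infer that the contrast is certain to be biased towards no harm. That needs women with cancer to score worse, and by enough, and the article gives no such figure. At a 5-point cancer effect the sign does not reverse anywhere in the range examined.

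Two further objections stand. The purpose of the contrast is inferred from the Discussion and is not stated where the contrast is planned. And a follow-up exam is not defined: if imaging after cancer treatment counted, some cancer patients would move into the follow-up group and the confounding would take another form, possibly in another direction.

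**Conclusion.** The point holds as a minor one. As printed, the comparison sets women with follow-up against a group containing nearly all the cancers, about 31% to 57% of that group over the assumed range. It therefore cannot separate the effect of waiting from the effect of a cancer diagnosis, and change from baseline does not repair this.

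The composition follows from the article's cancer share and diagnostic pathway, together with the assumed follow-up share and cancer share within that group. The size and direction of any distortion rest on assumed STAI effects: a 3-point waiting effect is shrunk by a 5-point cancer effect and is reversed only above about 5 to 11 points. The same reasoning applies to EQ-5D scores with the sign turned round. The primary endpoint and the randomised comparison of anxiety and QoL are untouched.

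**What to change.** State in the analysis plan that this comparison:

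- is restricted, in both groups, to women with no cancer or DCIS at work-up, saying whether a cancer found at the 6- or 12-month exam counts as found at work-up;
- counts only diagnostic follow-up after recall as a follow-up exam;
- adjusts for the baseline value of the score, arm, recall reason and recall BI-RADS;
- is labelled observational, with the conclusion on patient anxiety left to the randomised comparison, as already planned.

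The cost is a few sentences. Final diagnosis, baseline scores and the stratification factors are already recorded, so nothing new is collected. About 317 to 370 of the 528 women remain in the comparison.

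The loss of precision is smaller than that count suggests when follow-up is uncommon, because the women removed come almost entirely from the larger group. With equal standard deviations and no cancers in the follow-up group, the ratio of standard errors is as follows:

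- P = 0.30, f = 0.05 (26.4 women against 501.6, falling to 343.2): √[(1/26.4 + 1/343.2)/(1/26.4 + 1/501.6)] = 1.01.
- P = 0.40, f = 0.30 (158.4 against 369.6, falling to 158.4): √[(1/158.4 + 1/158.4)/(1/158.4 + 1/369.6)] = 1.18.

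The standard error thus rises by about 1% to 18%. Confounding by the imaging findings that led to follow-up is reduced by the adjustment but not removed, which is why the label matters.

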**Fig. 1 Fig1:**
[figure not shown]
**a** Schematic overview of an outcome specified in the five elements defined by Saldanha et al. [14]. **b**–**d** Five elements of the outcome of, respectively, the EQ-5D-5 L, STAI, and iMTA Productivity Costs Questionnaire (iPCQ)

To reduce patient effort, the questionnaires are offered digitally, or by telephone, if desired by the participant. Data from the digital questionnaires is automatically stored in the data management system.

### Informed consent and randomization protocol

All recalled women announced at one of the participating centers will be contacted for study participation. Written informed consent will be obtained and the first EQ-5D-5 L and STAI questionnaires regarding anxiety and current health state will be completed before any other study procedure is carried out. Participants are also asked for their consent to use their data in possible future studies. See Additional file 1 for the informed consent form in Dutch.

Women will be randomized to undergo standard of care (control arm) or CESM (intervention arm). Minimization with stratification factors will be applied in the computer-generated randomization screening and enrollment application software ALEA (version 3.0.2083.212r; ALEA Clinical, Abcoude, the Netherlands). Randomization will be stratified by the following: predominant reason for recall (mass, calcifications, asymmetry, architectural distortion), recall BI-RADS score (BI-RADS 0 versus BI-RADS 4/5), and study center. Enrollment in the four centers, including the master randomization file, will be overseen by the Study Coordinator. During the inclusion visit, written consent will be conducted and data entry will be done by one of the research team members in each center to execute randomization using ALEA. Should a problem occur in including a patient or randomization, the Study Coordinator must be reached so that he can provide assistance. After allocation, patient and radiologist will be informed about the outcome; hence, they are not blinded. However, the radiologist is blinded for the outcomes between the two groups, since the final diagnosis and pathology are not yet known. The outcome assessors and data analysts are blinded for the judgment of the next screening round by the screening radiologists, since accuracy also depends on the next screening round outcome. Each participant is assigned a trial identification number for anonymization, to analyze the data, and further to be used in publications. In each participant’s hospital patient file a statement will be noted about study participation and the assigned intervention or control group. On request, study participation can be ended during the follow-up phase.

### The control group: usual care with conventional breast imaging

Women undergoing standard of care will have their screening FFDM re-evaluated, adding (special) FFDM views, DBT, or US if deemed necessary. In FFDM and DBT, the breast is compressed between a paddle and detector plate. The laterality of the breast and views per breast depend on the judgment of the radiologist. At least one additional view of the recalled side will be performed. Tissue sampling (CNB, VAB, FNAC) can be recommended to support or to invalidate suspicious findings on imaging. In case of inconclusive findings, the radiologist can consider follow-up in 6 and/or 12 months or single breast MRI. The use of CESM is not permitted in this study arm.

### The experimental group: contrast-enhanced spectral mammography

CESM is based on visualizing angiogenesis in tumor tissue using dual-energy mammography [15]. Prior to image acquisition, an intravenous catheter will be placed in the antecubital vein, after which its patency will be checked by a saline test bolus. A non-ionic, low-osmolar contrast agent consisting of either iopromide (Ultravist® 300, Bayer Healthcare, Berlin, Germany) or iobitridol (Xenetix® 300, Guerbet, Villepinte, France) will be administered at a dose of 1.5 mL/kg body weight. If an automatic injector is used instead of manual administration, the injection rate will be 2.5–3 mL/s, followed by a saline flush. Image acquisition is started after at least 2 min after contrast administration [16]. Although there is a limited risk of complications, such as hematoma or incorrect catheter placement, a previous retrospective study showed that the risks of adverse reactions to the contrast agents and contrast-induced nephropathy are negligible [17]. Two days after CESM, the patient file will be consulted to investigate whether any late (serious) adverse reactions to the contrast agent have occurred that need medical treatment.

Similar to FFDM, the breasts are positioned between a mammography paddle and detector plate, and the four standard views are made: a cranio-caudal (CC) and mediolateral oblique (MLO) view of each breast. Special views can be requested by the reviewing radiologist. A typical CESM exam consists (per breast exposure) of two images: a low- and a high-energy image, which are acquired within seconds [18]. These images are used in post-processing to acquire the recombined image, which shows areas of contrast accumulation (Fig. 2). The CESM image acquisition needs to be completed within 10–12 min after contrast administration [19]. As in the control group, US, tissue sampling, MRI, and follow-up can be considered in case of inconclusive findings.

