Using CESM as a work-up tool also has some limitations. The most important disadvantages are the increased radiation dose and the administration of iodine-based contrast agents. Regarding the increase in radiation dose, several studies have shown that the mean radiation dose of CESM per exposure is in the range of 2.5-2.8 mGy [18, 31–33]. In comparison, the radiation dose of FFDM in these studies varied from 1.4 to 1.8 mGy. Jeukens et al. showed that the CESM radiation dose is approximately 80% higher than that in FFDM: 2.8 mGy versus 1.6 mGy, respectively [18]. Nevertheless, it is still within internationally accepted limits and does not substantially increase breast cancer incidence or mortality in women recalled from screening, who are at least 50 years. We believe that this increased dose is justified in the dedicated population as outlined. The chance of acquiring breast cancer due to this radiation exposure is expressed in the life attributable risk (LAR) numbers. For example, for a single view CESM acquisition having a mean radiation dose of 2.8 mGy per exposure, the LAR number for cancer incidence is 0.4 in 100,000 persons at the age of 60 years [34]. The LAR number for cancer mortality at this age is even 2–3 times lower. Some even advocate that there is no effect of radiation under a dose of 100 mSv. Hence, one may conclude that CESM exposure poses only a small additional risk compared to the lifetime risk for breast cancer incidence and mortality of 12,000 and 3000 cases per 100,000 women, respectively.

Regarding the use of iodine-based contrast, Houben et al. had in clinical practice in a similar population a low incidence (0.6%) of adverse hypersensitivity reactions [10]. In contrast, they also showed that occult cancers are being detected in 3–4% of the recalled women by using CESM. Consequently, the chance of finding occult (small) breast cancers is higher than the chance of having adverse reactions to contrast administrations (which are all documented in the RACER study), which in our opinion would justify the use of a CESM-based work-up of women recalled from screening.

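### The single day-2 file check for late contrast reactions does not support the statement that all reactions are documented, and it biases the trial's own late-reaction count downward

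*Protocol article*

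**What the plan says.** The Methods section on the experimental (CESM) group gives one step for finding late reactions: "Two days after CESM, the patient file will be consulted to investigate whether any late (serious) adverse reactions to the contrast agent have occurred". The sentence goes on to limit these to reactions that "have occurred that need medical treatment".

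The Discussion lists iodine-based contrast among the main disadvantages of CESM. It cites an earlier clinical-practice cohort with "a low incidence (0.6%) of adverse hypersensitivity reactions" and reports from the same source that "occult cancers are being detected in 3–4% of the recalled women by using CESM". It concludes that finding an occult cancer is likelier than having a reaction, and adds in parentheses that reactions to contrast "which are all documented in the RACER study".

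The section on primary and secondary outcomes does not list adverse reactions. It does say that all participants complete questionnaires "at six different time points (at study inclusion; after 2 and 4 weeks; and after 6, 12, and 18 months". These are offered digitally or by telephone.

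**The concern.** The check has three filters: a source (the patient file), a time (one look, at two days) and a severity threshold (treatment needed). The Discussion's statement has none. A site that follows the Methods to the letter would still leave the Discussion's claim unmet, because whole classes of late reaction fall outside the rule.

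At stake is what RACER can report about the harm of its own intervention. A reader told that all reactions were documented would take the final count as complete. So few reactions are expected that one or two missed cases could separate a report of some reactions from a report of none.

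**Working it through.** The documents give no figure for how completely reactions are captured, so the first step is a comparison of texts. The arithmetic after it is illustrative.

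**Step 1. Would the described check find the reaction?**

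| Late reaction | Found by the Methods check? | Covered by the Discussion's statement? |
|---|---|---|
| Treated, and in the hospital file by day 2 | Yes | Yes |
| Starts after day 2 | No | Yes |
| Needs no medical treatment | No | Yes |
| Self-treated | No, unless it happens to reach the file | Yes |
| Treated by the general physician, not in the file by day 2 | No | Yes |

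Every mismatch runs the same way, towards too few late reactions.

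**Step 2. Size of the CESM arm.** The sample size section gives 251 per group, so 2 × 251 = 502, and 502/0.95 = 528.4, stated as 528. With 1:1 allocation (inferred from the equal group sizes) and all allocated women examined, the CESM arm has 528/2 = 264 women.

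**Step 3. Expected events with complete capture.** At the cited 0.6%, 264 × 0.006 = 1.58 reactions. The chance of none is (1 − 0.006)^264 = 0.204, or 20%.

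**Step 4. Incomplete capture.** With capture share c (an assumption), the expected number recorded is 264 × 0.006 × c, and the chance of recording none is (1 − 0.006c)^264.

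| Assumed capture | Expected recorded | Chance of recording none |
|---|---|---|
| 100% | 1.6 | 20% |
| 75% | 1.2 | 30% |
| 50% | 0.8 | 45% |
| 25% | 0.4 | 67% |

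This applies c to the whole 0.6%. The Discussion does not limit that rate to late reactions, while the day-2 check concerns late reactions only. If some of the 0.6% are immediate reactions recorded on site, the loss is smaller than shown.

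**Step 5. What a count of zero would mean.** The exact two-sided 95% upper limit for 0/264 is 1 − 0.025^(1/264) = 1.39%. It is a valid limit for the true rate only if capture is complete.

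**Step 6. Could under-capture reverse the ordering of reactions and occult cancers?** A recorded 0.6% would have to hide a true 3–4%, which means capture of only 0.6/4 = 15% to 0.6/3 = 20%. Nothing in the documents suggests capture that low.

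**The case against.** The strongest reply is that this is a condensed article. The check concerns late reactions only. Immediate reactions may be recorded at the visit, and the full protocol may hold further safety procedures. That is fair, and silence on those matters is no finding. It does not remove the conflict, because the article states both the capture rule for late reactions and the claim of completeness, and the first does not support the second.

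The parenthesis might also mean only that reactions coming to attention are written down. If so, the wording is too broad and narrowing it settles the matter.

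Reactions are not a primary or secondary outcome, and no analysis described in the article uses their rate. That stands and limits the weight of the point.

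A reader might infer three stronger things that the documents do not support:

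- *That the benefit-harm argument rests on a biased rate.* Both its inputs, 0.6% and 3–4%, come from an earlier cohort, and RACER's recording cannot change either.
- *That the patient-friendliness claim rests on reaction counts.* The article ties it to fewer follow-up exams, less additional imaging and fewer days to diagnosis, with anxiety and quality of life measured.
- *That calling the risk negligible in the Methods contradicts 0.6% in the Discussion.* The Methods statement is "the risks of adverse reactions to the contrast agents and contrast-induced nephropathy are negligible", a qualitative summary of one retrospective study that also covers nephropathy. The 0.6% is a hypersensitivity rate from a differently cited source, and the article calls it low. The two are compatible.

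**Conclusion.** The point holds in a limited form. The described check does not support the statement that all contrast reactions are documented, and the two passages must be reconciled. Measured against all late reactions, RACER's own count will be biased downward. The direction follows from the rule itself; the size cannot be derived from the documents.

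The shift from a 20% chance of recording no reaction to 30%, 45% or 67% rests on 264 examined women, a 0.6% rate that is not specific to late reactions, and assumed capture shares. Even complete capture would leave the rate imprecise. The sample size, the primary analysis and the cited comparison of 0.6% with 3–4% are unaffected. The point is worth acting on because the remedy is cheap and improves what the trial can say about its own intervention.

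**What to change.** Keep the day-2 file check. Add one neutrally worded question to the existing 2-week (or 4-week) questionnaire on new complaints or care sought since the imaging exam, with the onset date.

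- Ask it in both arms, so that non-specific complaints have a comparator.
- Place it after the STAI and EQ-5D-5L, so that in an unblinded trial it does not colour the anxiety and quality-of-life answers.
- Record the exam date with it, because the questionnaires are timed from inclusion and not from the exam.
- Report the CESM-arm reaction rate with an exact 95% interval, and state that participants enrolled before the change have the file check only.

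If the question is not added, narrow the Discussion's statement to what the file check captures: late reactions requiring treatment that are in the patient file at two days.

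The cost is one question in a questionnaire already in use, the matching eCRF fields and a short amendment. Some non-specific complaints will need a causality note, and capture will differ between earlier and later participants. The change concerns data collection and wording only; no change to contrast administration or clinical management is proposed.
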